### Study objectives and outcome measures

The primary objective is to ascertain whether there are equivalent changes in HbA1c (primary outcome measure) in people with newly diagnosed T2DM allocated to either a urine or a blood glucose monitoring strategy over 18 months when incorporated as an integral part of a comprehensive self-management structured education programme (DESMOND).

The secondary objectives include: comparison of the two strategies on the secondary outcome measures over 18 months, including biomedical measures (systolic and diastolic blood pressure, lipid profile, body weight and waist circumference) and psychological measures (well being, anxiety, depression, treatment satisfaction and perceptions about diabetes) (for further details see Table 1). A qualitative sub-study will explore participant views about acceptability of, and preference for, the two self-monitoring methods included. An assessment of cost effectiveness will be conducted.

**Table 1 T1:** Biomedical and questionnaire measures used and time points in the trial

	Baseline	6 months	12 months	18 months

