### Presentation of the hypothesis

Our null hypothesis is that use of SMBG rather than urine monitoring in the context of delivering the DESMOND intervention will not be equivalent in terms of improving and sustaining glycaemic control over 18 months.

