### Testing the hypothesis

We will be measuring the equivalence of SMBG (and its cost-effectiveness) over a clinically relevant period of follow-up while controlling for the other components of a complex intervention, in particular, the educational programme itself and feedback of glucose levels from another form of monitoring.

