### Implications of the hypothesis

The DESMOND SMBG trial will provide additional evidence to inform the debate around the value of SMBG for people with T2DM not using insulin or at risk of hypoglycaemia. In particular it will allow us to assess whether SMBG is equivalent to urine monitoring in people with newly diagnosed T2DM who are undertaking a quality assured structured education course delivered in primary care.

If the null hypothesis is not rejected, then SMBG will not be recommended for people with newly diagnosed T2DM. However, if the null hypothesis is rejected, and the results demonstrate that SMBG is equivalent to urine monitoring in terms improving and sustaining glycaemic control over 18 months, then this will be used as evidence to recommend SMBG for people with newly diagnosed T2DM who are undertaking the DESMOND intervention.

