### Analysis

#### Power calculations and sample size

The aim is to show equivalence in mean HbA1c at 18 months of within ± 0.5%. Assuming a standard deviation (SD) at 18 months of 1.5%, [37] the sample size required without allowing for clustering for 80% power at 5% significance is 142 per arm. With an intra-cluster correlation of 0.05, [38] and an expected mean cluster size of 5, adjustment for clustering brings the number required to 170 per arm. Assuming 20% drop out and 20% non-consent, the numbers required are 266 referrals and 213 consents per arm.

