## Discussion

The DESMOND SMBG trial has been designed to provide additional evidence to inform the debate around the value of SMBG for people with Type 2 diabetes (T2DM) not using insulin or at risk of hypoglycaemia. Its particular strength is that it will allow us to assess the additional contribution of SMBG in people with newly diagnosed T2DM who are undertaking a quality assured structured education course delivered in primary care. Our hypothesis is that use of SMBG rather than urine monitoring in the context of delivering the DESMOND intervention will provide no added benefit in improving and sustaining glycaemic control over 18 months. Thus, we will be measuring any added benefit of SMBG (and its cost-effectiveness) over a clinically relevant period of follow-up while controlling for the other components of a complex intervention, in particular, the educational programme itself and feedback of glucose levels from another form of monitoring.

We will also compare the effect of the two self-monitoring methods on secondary outcome measures, including biomedical (systolic and diastolic blood pressure, lipid profile, body weight and waist circumference), and psychological (generic and disease specific well being, treatment satisfaction and perceptions about diabetes) measures. We will explore the views of participants concerning their experience of and preference for the two methods, and measure which self-monitoring strategy participants adopt over the subsequent 18 months. We will calculate the cost effectiveness of both methods.

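### The Discussion restates the two-sided HbA1c equivalence hypothesis as a one-directional claim that SMBG adds no benefit, and the same result can fail one and support the other

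*Protocol article*

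**What the plan says.** Most of the article asks a non-directional question.

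- Study objectives and outcome measures, on what the trial sets out to find: "The primary objective is to ascertain whether there are equivalent changes in HbA1c (primary outcome measure) in people with newly diagnosed T2DM".
- Presentation of the hypothesis, on what is to be rejected: "Our null hypothesis is that use of SMBG rather than urine monitoring in the context of delivering the DESMOND intervention will not be equivalent".
- Testing the hypothesis, on what is measured: "We will be measuring the equivalence of SMBG (and its cost-effectiveness) over a clinically relevant period of follow-up".
- Power calculations and sample size, on the margin: "The aim is to show equivalence in mean HbA1c at 18 months of within ± 0.5" (percentage points of HbA1c). The Abstract gives the same margin.

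The Discussion restates the hypothesis and what will be measured, in sentences that otherwise follow the two hypothesis sections closely, but with a different content:

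- On the hypothesis: "Our hypothesis is that use of SMBG rather than urine monitoring in the context of delivering the DESMOND intervention will provide no added benefit"
- On what will be measured: "Thus, we will be measuring any added benefit of SMBG (and its cost-effectiveness) over a clinically relevant period of follow-up"

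The Discussion does not mention equivalence, a margin or a test at this point.

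**The concern.** Equivalence fails if SMBG is materially better or materially worse than urine testing. A hypothesis that SMBG adds no benefit can fail only if SMBG is better. The sets of results that support each are therefore different, and the article publishes both as the trial's hypothesis.

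At stake is the primary conclusion. Once the data are known, a report could cite whichever published statement the result supports. Two situations matter:

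- SMBG turns out worse. Equivalence is not shown, but the Discussion's hypothesis is borne out.
- The difference is non-significant but imprecise. Equivalence is not shown, but the result could be presented as no added benefit because no significant benefit was found.

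**Working it through.** **Inputs** (Power calculations and sample size): margin ±0.5%, SD 1.5%, 80% power, 5% significance, intra-cluster correlation 0.05, mean cluster size 5, 142 per arm before and 170 per arm after clustering.

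**The plan's own figure.**
- n = 2 × (1.960 + 0.842)² × (1.5/0.5)² = 141.3, so 142 per arm.
- Design effect = 1 + (5 − 1) × 0.05 = 1.20, and 142 × 1.20 = 170.4, so 170 per arm.

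Both stated figures reproduce. This formula is the one for a two-sided difference test; one-sided 0.025 against a single 0.5% limit gives the same number. Two-sided equivalence with 80% power at a true difference of 0 would need 155 per arm before clustering (one-sided 0.05 on each side) or 190 (one-sided 0.025 on each side). The sample size therefore does not show which hypothesis was meant.

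**Planned precision.** SE = 1.5 × √(2 × 1.2/170) = 0.178. The half-width is 1.96 × 0.178 = 0.349 for a 95% CI and 1.645 × 0.178 = 0.293 for a 90% CI.

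**Example results** (SMBG minus urine; positive means HbA1c is higher with SMBG):

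| Observed | 95% CI | 90% CI | Within ±0.5? | No added benefit of SMBG? |
|---|---|---|---|---|
| 0.0 | −0.35 to 0.35 | −0.29 to 0.29 | yes, at either level | see note |
| +0.4 | 0.05 to 0.75 | 0.11 to 0.69 | no, at either level | supported |
| −0.3 | −0.65 to 0.05 | −0.59 to −0.01 | no, at either level | supported only if read as not significant at two-sided 5% |

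Note: at 0.0 the hypothesis is supported if it means excluding a 0.5% benefit or finding no significant benefit. It is not supported if the lower limit must lie above 0.

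The +0.4 row does not depend on how the Discussion is read. The lower limit is above 0, so it is also above −0.5, and there is no significant benefit. Nor does it depend on fine detail of the SE: for +0.4 to pass equivalence, the half-width would have to be below 0.5 − 0.4 = 0.1, against 0.349 or 0.293 at the planned size.

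**Power of the equivalence rule at a true difference of 0**: 2Φ(0.5/SE − z) − 1, with 0.5/SE = 2.805.
- 95% CI: 2Φ(2.805 − 1.960) − 1 = 0.602.
- 90% CI: 2Φ(2.805 − 1.645) − 1 = 0.754.

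**The case against.** The strongest answer is that the text which sets up the test is consistent. The Abstract, primary objective, null hypothesis, the section on testing it and the sample size aim all say equivalence. The Discussion sentence can be read as the authors' expectation in plain words. This stands as to weight: equivalence is the evident primary framing. It does not remove the conflict, because the sentence is labelled as the trial's hypothesis and is followed by a statement of what will be measured.

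A second answer is that practice would not change. In both situations described, equivalence fails, and Implications of the hypothesis then says: "If the null hypothesis is not rejected, then SMBG will not be recommended for people with newly diagnosed T2DM". A finding of no added benefit points the same way. This also stands, so the harm lies in the reported primary conclusion and not in the recommendation in those cases.

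A third answer is that the Discussion gives no decision rule, so a reader who calculates how often the two verdicts would disagree is supplying one. That is right. With a 95% CI, the disagreement is 20% (single 0.5% bound) or 37% (no significant benefit) at a true difference of 0. It is 61% or 63% if SMBG is truly worse by 0.2, and 2.5% or 43% if truly better by 0.2. So wide a spread shows that these figures illustrate assumed rules and do not measure a defect in the plan.

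Finally, the unstated sidedness of the 5% level is a detail that a condensed article may leave to the full protocol or analysis plan. It is not counted here.

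**Conclusion.** The point holds as an inconsistency in the stated hypothesis that should be corrected. A result with SMBG clearly worse, such as +0.4, fails the equivalence hypothesis and supports the Discussion's one. An imprecise non-significant result could be presented as the latter without meeting the former.

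The numerical example assumes the planning values: SD 1.5%, design effect 1.2 and 170 analysed per arm. It makes no allowance for the baseline adjustment and averaging over time described under Statistical analysis. The difference in direction between the two hypotheses does not depend on those values.

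Two stronger inferences are not supported. A reader might conclude that the trial has two competing primary hypotheses and no settled test; the consistency of the other sections argues against that. A reader might also take the 1.96 behind 142 per arm as fixing a 95% CI for equivalence; it does not, because that formula is for a difference or a single bound. The article does not state the CI level.

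**What to change.** - In the Discussion, replace the no-added-benefit hypothesis and the sentence on measuring added benefit with the equivalence hypothesis used under Presentation of the hypothesis and Power calculations and sample size. Name it as the only primary hypothesis.
- Add that a non-significant difference does not show that SMBG adds no benefit.
- Report any one-directional statement about SMBG as secondary, read from the relevant limit of the same confidence interval.
- State the CI level used for the equivalence decision, together with its power at a true difference of 0 at the planned size: about 60% with a 95% CI or about 75% with a 90% CI.

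The change is wording only and needs no new data or participants. It has two costs. A result favourable in one direction only can no longer be claimed as the primary conclusion. Stating the CI level with its power also makes visible that either level falls short of the stated 80%.

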## Endnote

^a^Randomisation was computed using the online resource at http://www.tufts.edu/~gdallal/randomize.htm.

## Abbreviations

SMBG: Self monitoring of blood glucose; T1DM: Type 1 diabetes; T2DM: Type 2 diabetes; HbA1c: Glycated haemoglobin; PCT: Primary care trust; DESMOND: Diabetes education and self management for ongoing and newly diagnosed; HCP: Healthcare professional.
